**<Control Group> Mini-Plate**

After laminoplasty, bone holes are created on both sides of the expanded lamina to place LAMINAclip2 (Olympus Terumo Biomaterial Corporation) screws, and the screws are placed.

Using dedicated instruments, place the plate: LAMINAclip2 (Olympus-Terumo Biomaterial Corporation) over the screw head and secure it.

The size of the screws and plates is determined according to the shape of the lamina in each case.

The number of plates used is specified as two or more.

[figure not shown]

[figure not shown]

[figure not shown]

**<Experimental Treatment Group> Suture-Anchor**

After expanding the lamina, place LAMIFIX (Olympus Terumo Biomaterial Corporation) anchors on the lateral masses on both sides of the expanded lamina. Secure the expanded lamina by suturing the suture thread connected to the anchor to the transected yellow ligament between the expanded lamina.

[figure not shown]

[figure not shown]

The number of suture anchors used is specified as two or more.

**7.1.4　Regarding Treatment Changes**

<When the Assigned Enlarged Laminar Retention Method Could Not Be Performed>

If the enlarged laminar retention method assigned at registration (mini-plate or suture-anchor) could not be performed for any reason, the attending surgeon shall perform dural decompression using the method they deem best. Prioritize the safety of the study subject and improvement of myelopathy, making appropriate judgments.

The reason the assigned laminoplasty with laminar fixation could not be performed and the laminoplasty with laminar fixation method actually performed must be entered in the case report form.

<If transitioning to posterior or anterior fusion>

If the attending surgeon determines significant cervical instability exists during surgery, or if it is deemed necessary to address intraoperative complications (e.g., laminar fracture, vertebral fracture), transition from laminoplasty to cervical posterior or anterior fusion. Prioritize the safety of the study subject, improvement of myelopathy, and spinal stability, making appropriate judgments.

- If transition to cervical fusion surgery occurs because laminoplasty was impossible, or if transition to cervical fusion surgery occurs before performing laminoplasty, the reasons must be documented in the case report form.
- For the patient in question, the study is discontinued (see 7.6), and surgery for DCM is performed using the settings and methods the surgical team deems optimal.

**7.1.5　Perioperative Management**

Perioperative management includes the type and duration of prophylactic antibiotics, preoperative and postoperative fluid management, timing of postoperative oral intake initiation and dietary content, wound and drain management, and postoperative cervical external fixation. The method of perioperative analgesic use should also follow the standard practice at each participating institution.

The presence or type of postoperative cervical external fixation is not specified, but details of any such fixation must be recorded in the case report form.

The timing of postoperative ambulation and the content of rehabilitation are not specified, but rehabilitation must be performed for all patients.

**7.1.6　Surveillance**

Postoperative investigations shall be conducted according to “7.2 Observation/Examination Items and Schedule”.

If surgical complications or other adverse events are identified, data for the items specified in 7.2.2 shall be collected and entered into the EDC system.

**7.1.7　Follow-up Treatment**

If the assigned expanded laminoplasty with anastomosis cannot be performed, subsequent treatment is not specified. However, the details of any treatment performed must be recorded in the case report form.

**7.2****Observation/Examination Items and Schedule**

**7.2.1　Observation/Examination Schedule**

The survey, observation, and evaluation items, along with the visit schedule for this study, are as follows.

|  | Pre-regist.  ~ Regist. | Surg. Date | PO 1 w | Discharge date | PO 30 d | PO 1y | PO 2 y |  |
| --- | --- | --- | --- | --- | --- | --- | --- | --- |
| Allowed Period |  |  |  |  | Within  ±14d | Within  ±56 d | Within ±56d | |
| Registration/Assignment | ● |  |  |  |  |  |  |  |
| Patient Background Information | ●※1 |  |  |  |  |  |  |  |
| Surgery (Protocol Treatment) |  | ● |  |  |  |  |  | |
| Surgery Information |  | ● |  |  |  |  |  |  |
| Intraoperative Complications/Adverse Events |  | ● |  |  |  |  |  |  |
| Early Postoperative Complications/Adverse Events |  |  |  |  |  |  |  |  |
| Medical History/Physical Examination | ●※1 |  | ● | ● | ● | ● | ● |  |
| JOA score | ●※1 |  |  |  |  | ● | ● |  |
| Cervical Plain X-ray  (Cervical Alignment) | ●※1 |  | ● |  |  | ● | ● |  |
| Cervical Plain CT  (Postoperative: Enlarged Laminar Retention Rate, Hinge Fracture/Bone Union) | ●※1 |  | ● |  |  | ● | ● |  |
| Cervical Plain MRI  (Paraspinal Muscle Cross-sectional Area) | ●※1 |  |  |  |  | ● | ● |  |
| Cervical Plain MRI  (Dural sac Area) | ●※1 |  |  |  |  | ● | ● |  |
| Cervical Plain MRI  (Grading of the mass posterior to the dural sac) |  |  |  |  |  | ● | ● |  |
| Late Postoperative Complications/Adverse Events |  |  |  |  |  |  |  |  |
| Health-Related QoL（EQ-5D） | ●※1 |  |  |  |  | ● | ● |  |
| Pain/Numbness Severity (VAS) | ●※1 |  |  |  |  | ● | ● |  |
| Cervical Disability Index (NDI) | ●※1 |  |  |  |  | ● | ● |  |
| Outcome Follow-up |  |  |  |  |  | ● | ● |  |
| Direct Medical Costs |  |  |  |  |  |  |  |  |

● ：Required

※1 : All surveys, observations, and tests related to this clinical study will be conducted after obtaining written consent from the research subjects. However, results from surveys, observations, tests, etc., performed as part of routine care prior to obtaining consent may be used as research data if they were conducted within 360 days prior to registration.

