**5.4　 Expected Participation Period for Study Subjects**

Expected participation period: Approximately 2 years

(Period from registration to surgery: Maximum 90 days; Follow-up period: 2 years post-surgery)

After the expected participation period ends, if any adverse events suspected to be related to the study are identified, follow-up will continue until the principal (or sub-principal) investigator determines the study subject's safety is assured. Note that this follow-up period shall not be included in the study period.

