# **７．****Matters Concerning Treatment for Study Participants**

## **7.1　Protocol Treatment Implementation Procedure**

**7.1.1　Informed Consent Acquisition**

• The attending surgeons shall confirm the subject's diagnosis and other eligibility criteria, provide a written explanation of this study, obtain the subject's understanding of the study, and acquire written informed consent from the subject.

• For tests conducted to determine eligibility, data obtained within 360 days prior to registration may be used, even if collected before consent acquisition.

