**7.1.3　Protocol Treatment**

- Protocol treatment (cervical laminoplasty) must be performed within 90 days of registration.
- If protocol treatment cannot be performed within 90 days for any reason, enter the reason for discontinuation in the case report form as “Protocol Treatment Discontinued”.
- If eligibility criteria are no longer met due to worsening of the primary disease or comorbidities between registration and the protocol treatment date (surgery date), the decision to continue study participation and perform surgery as protocol treatment is left to the discretion of the attending surgeon. The case report form must document that eligibility criteria were no longer met during the period from registration to the treatment date, along with details.
- Laminoplasty for DCM is performed using either the mini-plate or the suture-anchor.
- Surgery is performed under general anesthesia.
- A midline longitudinal skin incision is made from C2 to C7 in the prone position. Dissection is performed up to the medial facet joints.
- Perform a double-opening laminoplasty, expanding 2-4 laminae on the C3-6 vertebrae.
- Resect the tips of the spinous processes to expand the laminae. Use a high-speed drill to make a median longitudinal split in the midline of the laminae. Use the high-speed drill to create a groove at the medial aspect of the intervertebral joints, achieving a suitable hardness for lamina expansion. After creating a median longitudinal split and groove on all planned laminar expansions, gradually expand the lamina using a mucosal elevator. Medially transect the elevated ligamentum flavum, dissect adhesions to the dura mater, and confirm decompression by observing dura mater bulging. Control bleeding from the epidural venous plexus as needed.
- The attending surgeon shall perform the enlarged lamina fixation using either the plate method or the suture anchor method, according to the assignment results at registration.
- Dome-shaped laminectomy may be added to the cephalad and caudal laminae during lamina enlargement.
- Place a drain on the posterior aspect of the lamina prior to closure. Specifications and duration of drain placement are not stipulated.
- Regardless of any concomitant procedures, operative time, blood loss, and intraoperative/postoperative complications shall be included in the surgery. Details shall be recorded in the medical record (or surgical report) and case report.

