**8.2** **Evaluation and Recording of Assessment Indicators**

**＜Primary Endpoints＞**

Recovery rate in cervical JOA score before and after surgery

［Definition］

Use the cervical JOA score assessed by the surgeon before surgery and at postoperative 1 or 2 years. The recovery rate calculation formula is as previously reported^4)^, using the following formula:

Cervical JOA Score Recovery Rate = (Postoperative Score - Preoperative Score) / (17 - Preoperative Score) × 100 (%)

The primary analysis time point is postoperative 1 year. Results at postoperative 2 years are also presented as a final analysis.

The same applies to secondary endpoints 3) to 13).

[figure not shown]

Cervical JOA Score (Hirabayashi R et al: Japanese Orthopaedic Association Criteria for Evaluating Treatment Outcomes of Cervical Spinal Cord Disorders. J Orthop Surg Jpn, 68:[contact])

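### The baseline JOA, EQ-5D, VAS and NDI may be up to 450 days old at surgery, which can distort and blur the primary recovery rate in both arms alike

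*Protocol*

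**What the plan says.** - **Look-back.** In the Protocol 7.2.1 schedule, JOA, EQ-5D, VAS and NDI each have one preoperative mark, in the column that ends at registration, and none on the surgery date. Each mark carries note 1. The note's rule is that study assessments follow written consent; its exception is that earlier routine-care results "may be used as research data if they were conducted within 360 days prior to registration". Section 7.1.1 has a parallel allowance for eligibility tests: "data obtained within 360 days prior to registration may be used, even if collected before consent acquisition".
- **Wait for surgery.** Section 7.1.3: "Protocol treatment (cervical laminoplasty) must be performed within 90 days of registration". Section 5.4 agrees: "Period from registration to surgery: Maximum 90 days; Follow-up period: 2 years post-surgery".
- **Timing of the baseline JOA.** Section 8.2: "Use the cervical JOA score assessed by the surgeon before surgery and at postoperative 1 or 2 years". No window is attached to the preoperative score. The Overview also lists a preoperative clinical evaluation without a window. The 1-year and 2-year visits have a window of ±56 days.
- **Use of the score.** Recovery rate = (post − pre)/(17 − pre) × 100 (section 8.2). Preoperative JOA is also a covariate in the ANCOVA and the MMRM (10.5.2), and the recovery rate defines the 52.8% MCID endpoint (8.2, 10.5.3). EQ-5D, VAS and NDI are analysed as change from the preoperative value (10.5.3).
- **Disease course.** Section 3.1 describes a condition that progresses and is operated on once symptoms advance.

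**The concern.** The preoperative JOA enters the primary endpoint in both numerator and denominator, and then the model as a covariate. The protocol controls the date of the follow-up score to within 56 days but lets the other half of the formula be more than a year old. Because patients come to surgery when symptoms have advanced, an old score is more likely to be too high than too low. A baseline that is too high lowers the recorded gain and also shrinks 17 − pre, so the error grows as the baseline nears the ceiling.

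At stake are the recovery rates and MCID proportions that will be reported for each technique, and the precision of the non-inferiority comparison. This is a data-collection rule set in the protocol. A statistical analysis plan cannot restore a score that was never taken.

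**Working it through.** **1. Age of the baseline.** Look-back 360 days (7.2.1, note 1) plus wait 90 days (7.1.3, 5.4): 360 + 90 = 450 days. No other section shortens this for the four scores.

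**2. The plan's sample size.** Inputs from 10.2: margin 20, SD 40, one-sided alpha 0.025, power 0.9, true difference 0. The noncentral t gives 86 per arm, 172 in total (power 0.903). With 20% dropout, 172/0.8 = 215, or 216 as an even number. Both stated figures reproduce, and this point does not change them.

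**3. Effect on one patient**, using the protocol's formula and assumed scores:

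- JOA 10 at surgery, 14 at 1 year: (14 − 10)/(17 − 10) = 57.1%. With a recorded baseline of 12: (14 − 12)/(17 − 12) = 40.0%. The patient crosses the 52.8% threshold, and the shift is 17.1 points.
- JOA 9 at surgery, 13 at 1 year: 50.0%. Recorded baselines of 10, 11 or 12 give 42.9%, 33.3% or 20.0%.
- JOA 11 at surgery, 14 at 1 year: 50.0%. Recorded baselines of 12, 13 or 14 give 40.0%, 25.0% or 0.0%.

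**4. Effect on a group.** The documents give neither the share of old scores nor a rate of decline. Assumed: baseline JOA 10.5 ± 2.5, mean recovery 50%, and 25% of baselines too high by 1 or 2 points. Ranges cover simulation with and without rounding to whole JOA points.

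| Assumed recovery SD | No stale baselines: mean, SD | 1 point too high | 2 points too high |
| --- | --- | --- | --- |
| 30 | 49.4–49.5, 29.0–29.5 | 46.3–46.6, 31.5–32.6 | 42.0–42.3, 37.9–39.3 |
| 40 (rounded, truncated at 17) | 48.1, 36.9 | 44.9, 40.4 | 40.3, 47.7 |

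Mean recovery falls by about 3 points (48.1 − 44.9 = 3.2) or 7 to 8 points (48.1 − 40.3 = 7.8). For 1 point, the variance ratio is (31.47/28.99)² = 1.18, (32.6/29.5)² = 1.22 and (40.4/36.9)² = 1.20. For 2 points, it is (39.3/29.5)² = 1.77 and (47.7/36.9)² = 1.67. With recovery SD 30, about 10% (1 point) or 18% (2 points) of the patients with a stale score change MCID status.

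**5. Effect on power.** At 86 per arm, with ANCOVA on the recorded baseline and no true difference, power with no error, 1 point and 2 points is:

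- recovery SD 30: 0.996, 0.98, 0.92;
- recovery SD 40: 0.94, 0.89, 0.78.

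A repeat run agreed to within 0.02. For scale, an unadjusted comparison at 86 per arm has power 0.90, 0.83 or 0.74 if the endpoint SD is 40, 45 or 50.

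**The case against.** The strongest reply is that the trial's conclusion rests on a difference between arms. The scores are scheduled no later than registration, so their staleness cannot depend on allocation and is equal between arms in expectation. This stands. A reader might infer that old baselines bias the comparison or make non-inferiority easier to claim; the documents do not support either. In simulation with a true difference of −20 points (recovery SD 30), the false non-inferiority rate fell from about 3% to about 2% and 1% as the baseline error went from 0 to 1 and 2 points. An error in starting utility common to both arms also largely cancels from the incremental cost-effectiveness ratio.

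Three further replies have weight:

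- The planning SD of 40 exceeds both pilot SDs in 10.2 (22.8 and 32.9). With recovery SD 30, the planned 0.90 power survives even a 2-point error in a quarter of patients. It is lost only under the larger assumed SD.
- 450 days is the limit of an exception. Patients must already be scheduled for laminoplasty, and nothing shows how often old scores would be used.
- Section 7.1.3 does foresee change before surgery ("If eligibility criteria are no longer met due to worsening of the primary disease or comorbidities between registration and the protocol treatment date"), but that clause is about eligibility. No criterion contains a JOA threshold, so it is not evidence of JOA decline.

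The objection also constrains the remedy. The trial is open-label (5.2.1) and the surgeon scores the JOA (8.2). Re-scoring at the surgical admission could fall after allocation is known, exchanging error unrelated to arm for possible bias that is related to it.

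What the objection does not remove is the permission itself. No section tightens the window for the four scores, and later analysis cannot undo it.

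**Conclusion.** The point holds in a limited form. The protocol permits a baseline up to 450 days old for the primary endpoint and three patient-reported measures, in a disease it calls progressive. The expected harm is understated recovery and MCID proportions in both arms, added variance and a weaker covariate.

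The size rests on assumptions. If a quarter of baselines are 1 point too high, mean recovery drops about 3 points and variance rises about 20%. At 2 points, the drop is 7 to 8 points and variance rises by roughly 70%. Whether power falls below 0.90 depends on the true spread of recovery: it does not if the recovery SD is 30, and it does if it is 40 (0.89 or 0.78). If few old scores are used or JOA is stable, the effect is small. If old scores were too low, the direction would reverse.

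The sample size is not in error, and this is not a threat to the validity of the between-arm test. It is a loose rule that is cheap to tighten now and cannot be repaired later.

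**What to change.** - In note 1 (7.2.1), limit the 360-day allowance to imaging, background items and eligibility tests.
- Require JOA, EQ-5D, VAS and NDI to be scored after consent and before allocation, within a short stated window before registration, with the assessment date on the case report form.
- In 8.2 and 10.5.2, name that pre-allocation score as the one used in the recovery rate and as the covariate. This also settles which score counts when several exist.
- Where feasible, register close to surgery. Section 7.1.2 allows registration up to the day before, so the baseline can be recent without being scored after the allocation is known.

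With a window of W days before registration, the maximum baseline age becomes W + 90 days instead of 450, and less where registration is close to surgery. The cost is a footnote, a date field and a few minutes of scoring at the consent or registration contact. The target of 216 does not change.

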**7.2.2　Observation and Examination Items**

The observation and examination items for this study are as follows. The timing of implementation follows “7.2.1 Schedule”.

| Implementation Item | | Observation/Examination Item | |
| --- | --- | --- | --- |
| Consent Acquisition/Registration/Assignment | | Date of Written Consent Acquisition | |
| Patient Background Information | General Findings | Gender, Date of Birth, Physical Findings (Height, Weight, BMI), Smoking History,  Comorbidities, ASA (American Society of Anesthesiologists) Classification, Oral Medications (Antithrombotic Agents, Steroids, etc.), Occupation, Duration of Illness, History of Cervical Spine Surgery | |
|  | Clinical/Imaging Findings of DCM | Preoperative Diagnosis | CSM/OPLL |
|  |  | JOA score | 17 points |
|  |  | Health-Related QOL（EQ-5D） | 0-1 |
|  |  | Severity of Neck Pain, Upper Limb Pain, Upper Limb Numbness (VAS) | 0-100mm |
|  |  | NDI | Maximum score 50 |
|  |  | Plain X-ray | Cervical spine range of motion, sagittal balance (C2-7 angle, C-SVA, C7 slope),  For OPLL: Ossification lesion morphology (segmental/continuous/mixed), highest level and maximum ossification occupancy rate |
|  |  | MRI | Level of maximum stenosis, Level of T2 sagittal intramedullary signal change, C4/5 paraspinal muscle cross-sectional area (mm^2^) |
| Surgical Information | | Date of surgery, Participation of spinal surery specialist (None / Participated as surgeon / Participated as assistant), Surgical procedure (level of laminoplasty, Presence/absence of dome-shaped laminectomy), Operative time, Blood loss, method (mini-plate/suture-anchor), implant type (mini-plate/suture-anchor), implant size (length, dimensions), blood transfusion volume (intraoperative and up to 3 days postoperatively), type of hemostatic agent used, presence of drain, transition to cervical fusion (none/transition to posterior cervical fusion/transition to anterior cervical fusion) | |
| Intraoperative Complications/Adverse Events | | If any occur, record the complication name, outcome, response to the complication, relationship to cervical spine surgery, treatment details/date of treatment, and whether hospitalization was extended. | |
| Postoperative Course | | Type/presence/duration of postoperative external fixation  Admission date/discharge date → Postoperative hospital stay days, Outcome at discharge, Whether reoperation was performed during hospitalization | |
| Early Postoperative Complications/Adverse Events (within 30 days postoperatively) | | Confirm the presence of adverse events through medical history and physical examination.  If an adverse event occurs, document the event name, onset time, outcome, severity (including whether reoperation was required), relationship to cervical spine surgery, treatment details/date of treatment, and whether hospitalization was extended. | |
| Medical History/Physical Examination | | Conduct medical history and physical examination during regular postoperative outpatient visits. | |
| Plain X-ray | | Cervical spine (AP/Lateral/Anterior flexion lateral/Posterior flexion lateral): Confirm C2-7 angle/C-SVA/C7 slope  Full spine standing (AP/Lateral): Confirm SVA/Lumbar lordosis angle/Thoracic kyphosis angle/Pelvic incidence, check for existing vertebral fractures | |
| Cervical Plain CT | | Horizontal, sagittal, and coronal slices at each intervertebral level: Confirm presence of OPLL/Lamina retention rate, hinge fractures/gutter bone union. | |
| Cervical Plain MRI | | T2 and T1 sagittal/horizontal images  Preoperative: Maximum stenosis level, presence of intramedullary signal changes, C4/5 paraspinal muscle area, dural sac area  Postoperative: C4/5 paraspinal muscle area, dural sac area, Grading of the mass posterior to the dural sac | |
| Late Postoperative Complications/Adverse Events (From 31 days post-op to within 2 years post-op) | | If an adverse event occurs, document: event name, onset timing, severity, outcome, seriousness (whether reoperation required), relationship to cervical spine surgery, treatment details/date, and hospitalization status. | |
| Outcome Investigation | | Survival (Last confirmed survival date, presence/absence of death, date of death, cause of death)  Reoperation (Reoperation presence/absence, reoperation date, reason for reoperation, reoperation method)  Study Discontinuation (Discontinuation presence/absence, discontinuation date, reason for discontinuation) | |
| Direct Medical Costs | | Hospitalization Costs (Medical fees excluding surgery, surgery-related costs [surgery, surgical drugs, anesthesia, anesthetic drugs])  Outpatient Costs (Consultations, tests, drugs, other)  Hospitalization Re-treatment Costs for Adverse Events (Hospitalization medical fees excluding surgery, surgery-related costs [surgery, surgical drugs, anesthesia, anesthetic drugs])  Research collaborators collect the above costs from medical claims. | |

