Collect direct medical costs at the facility where surgery was performed for each patient at discharge, and at 1 and 2 years post-surgery. Direct medical costs include inpatient treatment costs and outpatient treatment costs for the following services, summing ①, ②, and ③.

① Inpatient treatment costs for DCM surgery (surgery-related costs [surgery, surgical drugs, anesthesia, anesthetic drugs]), excluding surgical fees

② Outpatient costs for DCM after the surgery date (consultations, tests, drugs, other)

③ Rehospitalization costs for adverse events (inpatient treatment fees excluding surgery, surgery-related costs [surgery, surgical drugs, anesthesia, anesthetic drugs])

The cost-effectiveness evaluation metric uses the Incremental Cost-Effectiveness Ratio (ICER). The ICER is calculated by subtracting the control group's costs from the trial treatment group's costs. (ICER). ICER is calculated by dividing the incremental cost—the difference between the trial treatment group's costs and the control group's costs—by the incremental effect—the difference between the trial treatment group's effect and the control group's effect.

The outcome measure used is QALY (quality-adjusted life year). QALY is calculated using a Markov model that accounts for patients requiring reoperation or experiencing death, based on QOL measured by EQ-5D. Utility values and cost values are discounted annually at a rate of 2%, as recommended by the Central Social Insurance Medical Council (https://c2h.niph.go.jp/tools/guideline/guideline_ja.pdf).

(15) Surgical complication incidence

Surgical complications are categorized into intraoperative, early postoperative (within 30 days after surgery completion [wound closure]), and late postoperative (from day 31 after surgery up to 2 years postoperatively) complication rates.

Mortality (all deaths during the study period) and reoperation rate within 2 years postoperatively are recorded independently for complications.

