**2) Surgical Complications**

Surgical complications in this study are defined as any undesirable or unintended illness or injury (including abnormal laboratory values) that occurs in study subjects in relation to the surgery performed as part of the protocol treatment. Surgical complications are classified as: general anesthesia complications; intraoperative complications (from the start of surgery to its completion [wound closure]); early postoperative complications (from completion of surgery [wound closure] to within 30 days postoperatively); and late postoperative complications (from 31 days postoperatively to within 2 years postoperatively). The evaluation period extends up to 2 years postoperatively.

When a surgical complication occurs, the complication name, outcome, management of the complication, severity, treatment details/date of treatment, and whether hospitalization was prolonged must be documented in the medical record and case report. Additionally, occurrence data must be periodically compiled and recorded in a monitoring report.

Severity is determined based on the Common Terminology Criteria for Adverse Events (CTCAE) version 5.0.

Grade 1: Mild, asymptomatic or mild symptoms, clinical or laboratory findings only, no treatment required

Grade 2: Moderate, requires minimal, localized, non-invasive treatment, limitations in activities of daily living beyond age-appropriate self-care

Grade 3: Severe or medically significant but not immediately life-threatening, requiring hospitalization or prolongation of hospitalization, incapacitation or inability to perform activities, limitation in activities of daily living

Grade 4: Life-threatening, requiring urgent intervention

Grade 5: Death due to the adverse event

1. **Serious Adverse Events and Surgical Complications**

The following are considered serious adverse events or surgical complications:

1) Death

2) Diseases or conditions that may lead to death

3) Diseases or conditions requiring hospitalization or extended hospitalization for treatment

4) Disability

5) Diseases or conditions that may lead to disability

6) Diseases or conditions deemed serious equivalent to 1) to 5)

7) Congenital diseases or abnormalities in subsequent generations

The evaluation period shall be up to two years post-surgery.

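### Section 7.2.2 ties the seriousness of late events to reoperation, which the section 9.1 criteria do not name, so a serious late event can be entered as non-serious

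*Protocol*

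**What the plan says.** Protocol section 7.1.6 (Surveillance) states that when a complication or other adverse event is found, the items in section 7.2.2 are collected and entered into the EDC system. Section 7.2.2 has a separate row for each time window:

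- **Intraoperative:** sites "record the complication name, outcome, response to the complication, relationship to cervical spine surgery", then treatment and any extension of the hospital stay. Neither severity nor seriousness is listed.
- **Early (within 30 days):** the list includes "severity (including whether reoperation was required), relationship to cervical spine surgery". There is no seriousness item.
- **Late (day 31 to 2 years):** the list includes "severity, outcome, seriousness (whether reoperation required), relationship to cervical spine surgery", and ends with "treatment details/date, and hospitalization status".

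Section 9.1 sets the definitions. Under surgical complications, "Severity is determined based on the Common Terminology Criteria for Adverse Events (CTCAE) version 5.0". Serious events are defined by seven criteria: death; a condition that may lead to death; "Diseases or conditions requiring hospitalization or extended hospitalization for treatment"; disability; a condition that may lead to disability; an equivalent condition; and a congenital disease or abnormality in later generations.

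Reoperation also appears elsewhere. The Outcome Investigation row of 7.2.2 records whether it happened, its date, reason and method. Section 8.2 (15) says that mortality and the "reoperation rate within 2 years postoperatively are recorded independently for complications", which I read as separately from the complication counts.

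**The concern.** The only item named seriousness in any of the protocol's event-recording lists is the late-event one, and its sole explanation is a test that 9.1 does not contain. Severity and seriousness are different concepts in 9.1, yet 7.2.2 attaches the same reoperation question to severity in one window and to seriousness in the next.

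This matters because the protocol seeks to show that suture anchors are not inferior in safety as well as efficacy (sections 1 and 4), and section 12.1 has serious adverse events monitored by group and by site. If sites use the parenthesis as the rule, a late event that meets a 9.1 criterion but needed no reoperation can be entered as non-serious. Whether a lasting deficit counts as disability is a judgement best made when the event is assessed. It is harder to settle from records at the end of follow-up.

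**Working it through.** No arithmetic is involved; the check is a comparison of texts.

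**Step 1. Does 7.2.2 govern what is entered?** Yes, by section 7.1.6. The other recording lists (8.2 for the three windows; 9.1 for adverse events, surgical complications and serious events) contain no item called seriousness. The 9.1 list for serious events does not ask which criterion was met.

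**Step 2. The three windows against 9.1.**

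| Window | Severity in 7.2.2 | Seriousness in 7.2.2 | Elsewhere |
| --- | --- | --- | --- |
| Intraoperative | not listed | not listed | 8.2 requires severity |
| Early | listed, with reoperation folded in | not listed | 8.2 requires severity |
| Late | listed | listed, explained by reoperation | 8.2 lists neither |

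The standard in 9.1 is a CTCAE grade for severity and the seven criteria for seriousness. The grade definitions printed in 9.1 do not turn on reoperation.

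**Step 3. How reoperation relates to the seven criteria.** None names it. A reoperation would ordinarily satisfy the hospitalization criterion, so it marks at most a subset of serious events. A yes to the parenthesis will usually agree with 9.1; a no proves nothing.

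**Step 4. Late events without reoperation, case by case.**

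| Late event, no reoperation | Under 9.1 | Literal answer to the 7.2.2 item | Other recorded fields that show it |
| --- | --- | --- | --- |
| Death | serious | no | outcome; Outcome Investigation row |
| Stroke with admission | serious (hospitalization) | no | hospitalization status, same row |
| Life-threatening event | serious | no | severity, if entered as CTCAE Grade 4 |
| Lasting paralysis, admitted | serious (disability, hospitalization) | no | hospitalization status, severity, outcome |
| Disability or risk of it, not admitted | serious (disability criteria) | no | severity and outcome only |

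The last line is the residual gap. Grade 3 in 9.1 covers incapacity as well as events that are severe but not disabling, so grade and outcome suggest disability without deciding the criterion.

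**Step 5. Is the exposed case foreseeable?** Yes. Table D in 8.2 names neurological symptoms and systemic complications as late events. Tables B and C, for the early window, already list observation as management for limb paralysis and conservative treatment for cerebral infarction. The protocol therefore expects grave events to be managed without reoperation.

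**Step 6. Where the field is used.** Section 10.5.3 (15) counts complications by period and assigned group, not by seriousness. The primary analysis in 10.5.2 uses only the JOA recovery rate. Section 12.1 lists serious adverse events by group and by site. Classification and monitoring are therefore where a wrong entry would show.

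**The case against.** The strongest reply is that the parenthesis is only an extra item to note. The early row supports this, since it reads "severity (including whether reoperation was required", where the reoperation question adds to severity and does not define it. Nothing says that 7.2.2 overrides 9.1, section 9.3.2 requires all serious adverse events to be reported, and the case report form itself is not among the documents. This stands as far as it goes: the reporting duty is intact and the intent may have been harmless. But the late row lacks the word that makes the early row additive, and a site entering data sees reoperation as the only explanation of the item.

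Four stronger readings are tempting, and the documents do not support them.

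- *A reader might infer that every late event without reoperation is coded non-serious.* The protocol does not say so. It permits that entry without requiring it.
- *A reader might infer that disability and life-threatening events would be lost.* Hospitalization status, severity and outcome sit in the same row, so admitted patients and Grade 4 events can be recovered, and many disabling events can be identified from grade and outcome.
- *A reader might infer that the comparison of arms on safety is biased, because an unblinded surgeon decides on reoperation.* The planned complication analysis does not use seriousness, and section 12.1 does not say that its serious-event table is built from this field. An effect that differs by arm is possible but not shown.
- *A reader might infer that section 11 makes the form the source for seriousness.* It does so only for listed data that the medical records lack, and it lists severity and degree, not seriousness.

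The missing intraoperative severity item is also partly mended by sections 8.2 and 9.1, which require severity in the medical record and case report.

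**Conclusion.** The point holds as an internal contradiction in a data-entry rule. Section 7.2.2 explains late seriousness by reoperation and folds reoperation into early severity; neither matches 9.1, and the intraoperative row omits both items. A late event that is serious under 9.1 can therefore be recorded as non-serious when no reoperation was required. The exposure is narrow: mainly disability, or a risk of it, with neither hospitalization nor reoperation.

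No proportion of misclassified events can be given, because the protocol states no expected rate of late serious events or of reoperations. The conclusion assumes that the EDC form follows the 7.2.2 wording, as 7.1.6 directs, and that at least some sites would read the parenthesis literally. The primary analysis, secondary endpoint 15 and the duty in 9.3.2 are unaffected. The correction is worth making before data entry because it is simple and the judgement is hard to reconstruct later.

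**What to change.** Reconcile section 7.2.2 with section 9.1:

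1. Use the same fields in the intraoperative, early and late rows: CTCAE version 5.0 grade, and serious yes/no by the 9.1 criteria, with the criterion met.
2. Delete the two reoperation parentheses in the early and late rows.
3. Keep reoperation as its own item, as the Outcome Investigation row already does and as section 8.2 (15) intends.
4. Align the recording lists in 8.2 and 9.1 with these fields, and build the serious-event table in 12.1 from the new yes/no field.

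The cost is protocol wording and a few fields in the electronic form. No visits, patients or analyses are added.
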